# Influence and mechanism of sodium-glucose cotransporter-2 inhibitors on the cardiac function: study protocol for a prospective cohort study

**DOI:** 10.3389/fendo.2023.1199960

**Published:** 2023-07-19

**Keywords:** cardiac function, cardiac mechanisms, SGLT2 inhibitors, prospective cohort study without control, diabetes

## Abstract

**Background:**

Acute myocardial infarction (AMI) poses a significant threat to cardiovascular diseases (CVDs), leading to a high risk of heart failure (HF) and cardiovascular death. Growing evidence has unveiled the potential of sodium-glucose cotransporter-2 (SGLT2) inhibitors to improve cardiovascular outcomes in patients with CVD regardless of diabetes, but there is limited evidence in AMI patients. Furthermore, it is controversial whether the effects can be ascribed to the amelioration of left ventricular (LV) function, which further complicates the understanding of their underlying mechanism.

**Methods:**

This study is a prospective, phase IV, open-label, parallel group, single-center trial conducted in a large tertiary teaching hospital in China. A total of 120 patients with AMI and type 2 diabetes mellitus (T2DM) will be included. Those who received SGLT2 inhibitors are considered as the experimental group, and those taking other antidiabetic agents are considered as the control group. The primary outcome is change in LV end-systolic volume index (LVESVi) measured by cardiac magnetic resonance (CMR) imaging from baseline during 1-year follow-up period. Secondary outcomes include other LV parameters such as LV mass, LV volume, and LV ejection fraction (EF); quality of life and functional capacity such as Kansas City Cardiomyopathy Questionnaire overall summary score (KCCQ-OS) and EuroQol-5 dimension (EQ-5D); biomarkers associated with diagnostic parameters of AMI and possible mechanisms on cardiovascular protection, such as creatine kinase, troponin T (TnT) level, troponin I (TnI) level, soluble suppression of tumorigenicity-2 (sST2), galectin-3 (Gal-3), fibroblast growth factor 21 (FGF21), and microRNA (miRNA) level.

**Discussion:**

This study aims to investigate whether SGLT2 inhibitors could improve LV function by measuring CMR, quality of life, and functional capacity in patients with AMI in real-world settings, providing evidence on the underlying mechanism of SGLT2 inhibitors on cardioprotection.

**Clinical trial registration:**

https://www.chictr.org.cn/showproj.html?proj=173672, identifier ChiCTR2200065792.

## Introduction

1

Type 2 diabetes mellitus (T2DM) is an independent and strong risk factor for cardiovascular events, exhibiting a double increased susceptibility to cardiovascular diseases (CVDs) when compared to individuals without T2DM (1, 2). Sodium-glucose cotransporter-2 (SGLT2) inhibitors (SGLT2i) are initially used as glucose-lowering agents in T2DM patients with CVD. The emergence of substantial cardiovascular outcome clinical trials investigating SGLT2i, such as empagliflozin (EMPA-REG OUTCOME) (3), dapagliflozin (DECLARE-TIMI 58) (4), canagliflozin (CANVAS Program) (5), ertugliflozin (VERTIS CV) (6), and sotagliflozin (SCORED) (7), has demonstrated the effects of SGLT2i on the reduction of the occurrence of cardiovascular events and hospitalization for heart failure (HF) in T2DM patients with high risks for CVD or chronic kidney disease (CKD). From the angle of underlying mechanisms, long-term exposure to hyperglycemia affected signaling pathways inducing electrical disturbances in cardiomyocytes and mitochondrial dysfunction, prompting elevated reactive oxygen species (ROS) production and even apoptosis (8, 9). Preclinical data demonstrated (10, 11) that SGLT2i inhibit Na^+^/hydrogen exchanger 1 (NHE-1), leading to a reduction of Na^+^ in cardiac cytoplasm whose high expression was considered as a denominator of diabetes and HF and increasing Ca^2+^ level in cardiac mitochondria to improve ATP generation and viability of cardiomyocytes. Another explanation for the benefit in cardiomyocytes is that empagliflozin could reduce Ca^2+^/calmodulin-dependent kinase II (CaMKII) activity in both HF murine and human ventricular cardiomyocytes to improve contractility, since increased CaMKII levels are considered as hallmarks of HF (12). Moreover, several mechanistic investigations (13) also focused on its cardiovascular protective effects encompassing improvement in myocardial efficiency and endothelial function and reduction of oxidative stress, fibrosis, and inflammation of the heart. Thus, the recent guideline strongly recommends patients with T2DM and CVD to receive SGLT2i whether they are treatment-naive or already on metformin (14).

Acute myocardial infarction (AMI) poses a significant threat to CVDs, leading to a high risk of HF occurrence and cardiovascular death (15–17). Although patients receive updated evidence-based therapies early post-infarction, the contemporary rates of adverse cardiovascular outcomes remain high (18, 19). Recent preclinical studies (20, 21) in AMI mice treated with SGLT2i demonstrated new mechanistic insights into the reduction of infarction size and cardiomyocyte apoptosis, while data from clinical trials are still lacking in AMI. Thus far, conflicting outcomes were reported in studies on cardiac function with SGLT2i, likely stemming from factors such as limited sample size, short follow-up periods, and variations in patient characteristics (22–26). In our prior meta-analysis involving 13 trials and involved 1,437 participants, we observed that SGLT2i could improve LV function, and most studies focused on empagliflozin or HF patients (26). In this study, we present a protocol to assess the effects of SGLT2i on cardiac function in AMI patients. Meanwhile, other outcomes, including quality of life, functional capacity, and potential mechanisms, will also be discussed.

## Materials and methods

2

### Study design and setting

2.1

This is a prospective, phase IV, open-label, parallel group, single-center trial in patients with T2DM and AMI. The purpose of this trial is to assess the effect of SGLT2i on cardiac structure and cardiac function in these high-risk patients. Furthermore, we will evaluate the quality of life and other dimensions in these high-risk HF populations by questionnaire’s instructions [Kansas City Cardiomyopathy Questionnaire overall summary score (KCCQ-OS) and EuroQol-5 dimension (EQ-5D)]. Finally, biomarkers associated with diagnostic parameters of AMI [creatine kinase, troponin T (TnT), troponin I (TnI)], the potential mechanism on cardiovascular protection associated with the biomarkers [soluble suppression of tumorigenicity-2 (sST2), fibroblast growth factor 21 (FGF21), galectin-3 (Gal-3)], and microRNA (miRNA) level will be explored. The trial is registered by School of Medicine, Shanghai Jiao Tong University (Trial Registration: ChiCTR2200065792).

### Inclusion and exclusion criteria

2.2

#### Inclusion

2.2.1

(I) Men and women aged 18–80 years with T2DM and AMI undergoing successful percutaneous coronary intervention (PCI) within 14 days of hospital admission;

(II) treated with at least one antidiabetic drug besides lifestyle interventions;

(III) estimated glomerular filtration rate (eGFR) ≥45 mL/min/1.73 m^2^;

(IV) diagnosed with either ST-elevation myocardial infarction (STEMI) or non-ST elevation myocardial infarction (NSTEMI) according to the Fourth Universal Definition of Myocardial Infarction (27) and T2DM diagnosed based on the guideline for the prevention and treatment of T2DM in China (2020 edition) (28).

(V) Severe myocardial necrosis with a rise in CK >800 U/L and a TnT level or TnI level >10× upper limit of normal (ULN) after AMI (29, 30).

#### Exclusion

2.2.2

(I) Patients with poor compliance;

(II) History of new-set AMI over 2 months.

(III) eGFR <45 mL/min/1.73 m^2^ or on dialysis (derived using CKD EPI);

(IV) currently pregnant or lactating women.

The detailed eligibility and exclusion criteria are provided in **Table 1**.

**Table 1 T1:** List of inclusion and exclusion criteria.

Inclusion criteria
1. Men and women aged 18–80 years with T2DM and AMI undergoing successful percutaneous coronary intervention (PCI) within 14 days of hospital admission
2. Diagnosed with either ST-elevation myocardial infarction (STEMI) or non-ST elevation myocardial infarction (NSTEMI) according to the Fourth Universal Definition of Myocardial Infarction
3. Severe myocardial necrosis with a rise in creatine kinase >800 U/L and a troponin T (TnT) level or troponin I (TnI) level >10× upper limit of normal (ULN) after AMI
4. Diagnosed with T2DM based on the guideline for the prevention and treatment of type 2 diabetes mellitus in China (2020 edition)
5. eGFR ≥45 mL/min/1.73 m^2^
6. Treated with at least one antidiabetic drug besides lifestyle interventions to lower blood glucose
7. Capable of offering signed informed consent and understanding the protocol
8. Good Adherence: Having good compliance (taking more than 80% of monthly pill count), being able to understand, perform, and agree to the prescriber physician’s instructions
Exclusion criteria
1. Currently pregnant or lactating women
2. History of new-onset AMI over 2 months
3. eGFR <45 mL/min/1.73 m^2^ or on dialysis (derived using CKD EPI)
4. Cognitive impairment and failure to complete scheduled follow-up
5. Any contraindication to CMR procedures

AMI, acute myocardial infarction; STEMI, ST-elevation myocardial infarction; NSTEMI, non-ST elevation myocardial infarction; T2DM, type 2 diabetes mellitus; eGFR, estimated glomerular filtration rate.

### Intervention

2.3

Patients with T2DM will continue the previous glucose-lowering regimen unless glycemic control deteriorates requiring regimen to be adjusted. Patients who received SGLT2i are considered as SGLT2 inhibitors group, and patients not taking any SGLT2i are considered as non-SGLT2 inhibitors group (control group). Based on the requirement of open-label study, patients will be assigned to a 1-year treatment with either SGLT2i (empagliflozin 10 mg/day or dapagliflozin 10 mg/day or canagliflozin 100 mg/day) or other antidiabetic drugs [insulin, metformin, α-glucosidase inhibitors, sulfonylurea hypoglycemic agents, dipeptidyl peptidase-4 inhibitors (DPP4i), glucagon-like peptide-1 (GLP1) receptor agonists, and so on] (31). Patients without SGLT2i contraindication were prescribed one type of SGLT2i, other patients used other antidiabetic drugs in order to maintain the blood glucose into the target in the hospitalization (fasting blood glucose 7.8–10 mmol/L, postprandial blood glucose 7.8–13.9 mmol/L) (31). Considering the beneficial effects on LV function and high availability in China (26), empagliflozin was recommended first. Participants with contraindications of SGLT2i including those with the presence of ketone bodies or genitourinary infections might be assigned to the control group without SGLT2i. Of note, DPP4i (saxagliptin or sitagliptin) and thiazolidinediones (such as rosiglitazone or pioglitazone) are not preferred in patients with AMI combined with HF, which may worsen HF and cause hospitalization based on the present guideline (32).

Patients will participate in three visits (at 3, 6, and 12 months after hospitalization for new-onset AMI) in 1 year (see **Figure 1** for an overview of all visits’ process).

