### CMR and analysis

2.5

Contrast-enhanced CMR will be performed on a clinical 3.0-Tesla scanner (Achieva TX, Philips Healthcare, Best, Netherlands) within 14 days after the first PCI and at 1-year follow-up. All images will be obtained in breath-hold with a default field of view of 350 × 350 mm^2^. An experienced reader blinded to clinical data will analyze the CMR image with commercially available software (QMassx MR 7.5, Medis Medical Imaging, Leiden, Netherlands). The endocardial contour of the LV will be delineated excluding trabeculations and LV papillary muscles. In cases with significant discrepancy, the contours will be reviewed and corrected by a consensus group. Quantitative detection of LV volume and LVEF will be calculated based on short-axis slices of cine images covering the whole heart at end systole and end diastole, respectively. The extent of both infarction and microvascular obstruction will be semiquantified as a percentage of LV myocardial mass (% LVM).

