#### Sample size calculation

2.8.1

The sample size of this trial is calculated based on the primary outcome—the change in LVESVi. In a recent randomized controlled trial (SUGAR-DM-HF), the mean ± standard deviation (SD) of change in LVESVi in the experimental group and control group was -7.9 ± 11.8 mL/m^2^ and -1.5 ± 11.3 mL/m^2^, respectively (24). These data were for an 80% power at a 2.5% significance level [α = 0.025] with a 1% margin of error. Sample size was calculated to be 108 patients randomly assigned 1:1 to empagliflozin 10 mg once daily or placebo (24). Considering a 10% dropout in our previous study due to the presence of dressing change or medication nonadherence, a sample size of 120 subjects (two groups of 60) is necessary.

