#### Statistical analysis

2.8.2

Continuous variables will be described as mean with SD and compared by unpaired Student’s t-tests or Mann–Whitney U tests. Categorical variables of baseline characteristics will be summarized using count statistics, presented as percentage n (%) as appropriate. Chi-square test will be used when sample size is larger than 40; Fisher’s exact test will be used when sample size is smaller than 40. The results with p values <0.1 in univariate regression or considered meaningful in clinical practice will be further analyzed using multivariate regression to explore the effects of SGLT2i on LV function. All analyses will be conducted using the SPSS software, version 22.0 (SPSS Inc., Chicago, IL, USA).

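### Section 2.3 gives two rules for choosing SGLT2i treatment that conflict if read literally; on the kinder reading, treatment follows contraindication and the LVESVi comparison may lack eligible controls

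*Protocol article*

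**What the plan says.** Section 2.3 (Intervention) makes four statements about treatment in one paragraph:

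- "Patients with T2DM will continue the previous glucose-lowering regimen unless glycemic control deteriorates requiring regimen to be adjusted".
- Group membership goes by receipt: "Patients who received SGLT2i are considered as SGLT2 inhibitors group, and patients not taking any SGLT2i are considered as non-SGLT2 inhibitors group".
- "Patients without SGLT2i contraindication were prescribed one type of SGLT2i, other patients used other antidiabetic drugs". This sentence is tied to glucose targets during the hospital stay.
- Participants with a contraindication, with ketone bodies and genitourinary infection as examples, "might be assigned to the control group without SGLT2i".

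The purpose in section 2.1 is "to assess the effect of SGLT2i on cardiac structure and cardiac function in these high-risk patients". Table 1 requires at least one antidiabetic drug and does not exclude patients already on an SGLT2i. CMR is done "within 14 days after the first PCI and at 1-year follow-up" (section 2.5). Section 2.8.1 takes its effect and SDs from a randomised, placebo-controlled trial of empagliflozin with 1:1 allocation and concludes that "a sample size of 120 subjects (two groups of 60) is necessary". In section 2.8.2, variables that pass a univariate screen or are "considered meaningful in clinical practice will be further analyzed using multivariate regression to explore the effects of SGLT2i on LV function". The limitations paragraph of the Discussion relies on these analyses for the credibility of the results.

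**The concern.** The study is not randomised, so the treatment rule decides who is compared on the primary endpoint. A patient stable on metformin with no contraindication stays off the SGLT2i under the first sentence and receives one under the third. The grouping by receipt is clear once treatment is known, but the paragraph does not settle how treatment comes about.

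If the prescribing sentence governs, its remaining patients are, by grammar, those with a contraindication. The difference in LVESVi change could then reflect who can take the drug as well as what the drug does. Regression can separate the two only where eligible patients are found in both groups. Recruiting each group to 60 fixes the counts but not this overlap.

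A smaller matter follows from the continue rule. Patients already on an SGLT2i can enter the treated group with a baseline scan taken on the drug, so the group may mix continued use with new use.

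**Working it through.** **Reading the two rules together**

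| Patient | Continue rule | Prescribing rule |
|---|---|---|
| Stable on another drug, no contraindication | stays off SGLT2i: control | SGLT2i group |
| Stable on another drug, contraindicated | control | control |
| Already on SGLT2i, no contraindication | SGLT2i group, baseline scan on drug | SGLT2i group |

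The rules disagree in the first row. If the continue sentence covers only background drugs, or only the time after discharge, the first row follows the prescribing rule and the conflict goes. Contraindicated patients are then the only controls that the paragraph identifies.

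**The plan's own sample size.** Inputs from section 2.8.1: changes of -7.9 (SD 11.8) and -1.5 (SD 11.3) mL/m², alpha 0.025, power 80%, dropout 10%.

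- Difference = 7.9 - 1.5 = 6.4.
- Reading alpha as one-sided (the same as two-sided 5%) and using SD 11.8: n per group = 2 × (1.96 + 0.84)² × 11.8² / 6.4², which rounds up to 54, so 108 in all.
- 108 / 0.9 = 120.

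The stated figures reproduce, so the arithmetic is not at issue.

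**Reference power.** Pooled SD = √((11.8² + 11.3²)/2) = 11.55. With 54 evaluable per group, SE = 11.55 × √(2/54) = 2.22, and power for 6.4 at two-sided 5% is 82%.

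**Illustration of reduced overlap.** Assume that a share q of the 54 controls is contraindicated, that no SGLT2i patient is, and that the model contains treatment and contraindication. The treatment effect is then estimated from 54 treated patients and 54(1 - q) eligible controls:

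Var = SD² × [1/54 + 1/(54(1 - q))]; inflation over the plan = [1 + 1/(1 - q)]/2.

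| q (assumed) | Eligible controls | Inflation | SE | Power, two-sided 5% |
|---|---|---|---|---|
| 0 | 54 | 1.0 | 2.22 | 82% |
| 50% | 27 | 1.5 | 2.72 | 65% |
| 75% | 13.5 | 2.5 | 3.52 | 44% |
| 90% | 5.4 | 5.5 | 5.21 | 23% |
| 100% | 0 | – | – | not estimable |

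**If contraindication is left out of the model.** If contraindicated controls differ from eligible ones by g mL/m² in mean change, the unadjusted difference is biased by q × g. For example, q = 50% and g = 4 give a bias of 2 mL/m². With SE 2.22, that raises the false-positive rate from 5% to about 15% when the drug has no effect. If g = 0 there is no bias, and no reason to adjust.

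The protocol states neither q nor g. Both are assumptions here.

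**The case against.** The strongest reply is that the paragraph describes a sequence: SGLT2i prescribing in hospital, then maintenance of the regimen. The prescribing sentence does refer to the hospital stay, and the patient-flow figure, which is not available here, may make this plain. That reply can remove the contradiction. It does not remove the link between treatment and contraindication, because it leaves the prescribing rule in charge.

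A second reply is that nothing makes contraindicated patients the bulk of the controls. This stands. A reader might infer that controls come largely from them, but the wording on assigning them is permissive, controls are defined only by not taking the drug, and refusal or physician choice could supply others.

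A third reply is that a variable which drives treatment but not outcome is no confounder. This also stands. The documents do not say that ketone bodies or genitourinary infection predict LVESVi change. If they do not, 54 versus 54 keeps its 82% power. A reader might take the power table as a forecast, but it needs both an assumed share and a prognostic effect that is not shown.

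On prior users, a reader might conclude that their inclusion invalidates the comparison. The documents do not support that. Their change still covers a year of use after the infarct, which fits the purpose in section 2.1; early initiation is raised only in the Discussion; and new users may also be scanned after starting the drug, given the 14-day window. No size can be put on this limb.

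**Conclusion.** The point holds in a limited form. Read literally, section 2.3 gives a stable, eligible non-user two different treatments. On the reading that removes the conflict, treatment is tied to contraindication, and the only source of controls the paragraph names is contraindicated patients. The primary LVESVi difference may therefore set eligible against contraindicated patients. If contraindication matters for LVESVi change, the planned regression can repair this only to the extent that eligible non-users are enrolled.

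The fall from 82% to 65% at q = 50% shows the mechanism. It rests on an assumed share, on contraindication being prognostic and in the model, and on two-sided 5%, the level at which the plan's 108 reproduces. A reader might go further and say that no interpretable contrast is possible under either rule. The documents do not show that, because eligible patients may be found in both groups. Nor is the non-randomised design itself the fault, since the title declares a cohort study. The point deserves correction because it concerns who is compared on the primary endpoint, although its size is unknown.

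**What to change.** - **Section 2.3:** replace the two sentences with one rule. Background glucose-lowering drugs continue in both groups, and SGLT2i use follows the choice of physician and patient.
- **Data collection:** record any SGLT2i contraindication, the reason for the treatment choice, and SGLT2i use before the index infarction.
- **Section 2.8.2:** include baseline LVESVi, which is already collected, as a covariate in the primary comparison. Prespecify an analysis restricted to SGLT2i-eligible patients and a sensitivity analysis without prior users.
- **Reporting:** if controls prove to be mainly contraindicated patients, present the difference as descriptive and not as an SGLT2i effect.

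The cost is a short amendment and a few extra data items. The restricted analysis will be less precise, and eligible non-users may be few, since the Introduction reports a strong guideline recommendation for SGLT2i in these patients. Confounding by indication remains when treatment follows choice. Excluding all prior users, or counting only eligible patients toward the two groups of 60, would go further but is debatable, because it could slow recruitment at a single center.

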### Endpoints

2.4

The primary endpoint is the change of cardiac function [LV end-systolic volume index (LVESVi)] measured by cardiac magnetic resonance (CMR) in T2DM patients with AMI. The secondary endpoints are (I) other changes in parameters of cardiac function measured by CMR and echocardiography (LVEF, LV mass, LV volume); (II) change in KCCQ-OS and EQ-5D from baseline; (III) change in biomarkers related to myocardial parietal stress [N-terminal fragment brain natriuretic peptide (NT-pro BNP)], myocyte injury (creatine kinase, TnI, TnT), fibrosis (sST2, Gal-3), inflammation including interleukin-1β (IL-1β), interleukin-6 (IL-6), interleukin-8 (IL-8), interleukin-10 (IL-10), tumor necrosis factor-α (TNF-α), procalcitonin (PCT), C-reactive protein (CRP), and FGF21 in hospital laboratory research, as well as miRNA level. The detailed endpoints are provided in **Table 2**.

**Table 2 T2:** Trial endpoints.

	Outcome measures
Primary endpoint	
Cardiac function in T2DM patient with AMI 12 months after the event	Change in LVESVi from baseline to the study end at 12 months measured by cardiac MRI
Secondary endpoints	
1. Parameters of cardiac structure	Change in LVEF, LV mass, LV volume at 3 months, 6 months, and 12 months after hospitalization for new-onset AMI
2. Biomarkers related to myocardial parietal stress 3. Biomarkers related to AMI 4. Biomarkers related to fibrosis 5. Biomarkers related to inflammation	Change in NT-pro BNP; Change in CK, TnI, TnT; Change in sST2, Gal-3; Change in IL-1β, IL-6, IL-8, IL-10, TNF-α, CRP, and PCT; at 3 months, 6 months, and 12 months after hospitalization for new-onset AMI
6. Questionnaire’s instructions on health status	Change in KCCQ-OS and EQ-5D at 3 months, 6 months, and 12 months after hospitalization for new-onset AMI
Exploratory endpoints on the mechanisms	
To investigate that whether SGLT2i will have an effect on miRNAs and FGF21	Change in miRNAs and FGF21

AMI, acute myocardial infarction; LVESVi, LV end-systolic volume index; MRI, magnetic resonance imaging; eGFR, estimated glomerular filtration rate; SGLT2i, sodium-glucose cotransporter-2 inhibitor; LV, left ventricular; EF, ejection fraction; NT-pro BNP, N-terminal fragment brain natriuretic peptides; CK, creatine kinase; TnI, Troponin I; TnT, Troponin T; sST2, soluble suppression of tumorigenicity-2; Gal-3, galectin-3; KCCQ-OS, Kansas City Cardiomyopathy Questionnaire overall summary score; EQ-5D, EuroQol- 5 dimension; FGF21, fibroblast growth factor 21.

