#### Blood samples

2.7.1

Blood samples for routine biomarkers (NT-pro BNP, creatine kinase, TnI, TnT, sST2, IL-1β, IL-6, IL-8, IL-10, TNF-α, CRP, PCT, Gal-3) will be collected and measured by the hospital laboratory service from the eligible patients within 14 days after AMI incidence and at 1-year follow-up. A total of approximately 8 mL of blood samples will be drawn from the antecubital vein into two vacuum blood collection tubes at two time points: on the first 14 days of AMI (admission) and at 1 year following AMI. To obtain plasma, 4 mL of blood sample with anticoagulants (EDTA) will be centrifuged at 3,000 rpm for 10 min at 4°C, then the yellow cell-free supernatant will be collected and frozen in RNase-free Cryo-Tubes under -80°C until further processing. To obtain serum, the tubes without anticoagulants within 4 mL of peripheral blood samples are let stand at a 45- to 60-degree angle under 4°C for at least 1 h to promote coagulation. Then, the blood is centrifuged within 10 min of withdrawal at 3,000 rpm for 10 min to obtain the serum, which will be separated into RNase-free tubes. The handled samples are stored under -80°C to be used further for the miRNAs and FGF21 detector.

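### Genitourinary infection is a named route into the control group, and the baseline inflammation markers are drawn in the same window, so controls may show a larger fall that is not a drug effect

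*Protocol article*

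**What the plan says.** **Allocation (2.3 Intervention).** There is no randomisation step. The general rule is that "Patients without SGLT2i contraindication were prescribed one type of SGLT2i, other patients used other antidiabetic drugs". Among patients with a contraindication, "those with the presence of ketone bodies or genitourinary infections might be assigned to the control group without SGLT2i". No expected number or share of such patients is given.

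**Eligibility (2.2.2 and Table 1).** The exclusions cover compliance, timing of the infarction, renal function, pregnancy or lactation, contraindication to CMR, and "Cognitive impairment and failure to complete scheduled follow-up". Infection is in neither list.

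**Endpoint (2.4, Table 2).** One group of secondary endpoints is "Change in IL-1β, IL-6, IL-8, IL-10, TNF-α, CRP, and PCT".

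**Sampling (2.7.1 Blood samples).** Blood for these markers is taken "from the eligible patients within 14 days after AMI incidence and at 1-year follow-up". Table 2 also lists changes at 3 and 6 months, for which 2.7.1 describes no draw. The two places need to be reconciled, but the present point needs only the baseline and 1-year samples.

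**Analysis (2.8.2).** Continuous variables are "compared by unpaired Student’s t-tests or Mann–Whitney U tests". Variables that pass a screening step "will be further analyzed using multivariate regression to explore the effects of SGLT2i on LV function". No adjusted analysis is stated for the inflammation markers.

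**The concern.** In this design the variable that helps to decide the group can itself raise the baseline value of the outcome. A patient with a genitourinary infection during the index admission may be steered to control, remains eligible, and gives the baseline sample in that same period. If the infection raises CRP, procalcitonin or a cytokine and has cleared by 1 year, the patient's change score contains recovery from infection as well as recovery from infarction. Patients in the SGLT2i group are less likely to contribute that component, because infection is a stated reason for not being in that group.

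The direction is predictable: a larger fall in controls. A real anti-inflammatory effect of SGLT2i could be hidden or could appear reversed. This goes beyond ordinary baseline imbalance. If infection status is not recorded at the draw, no later analysis can separate infection from infarct-related inflammation. Adjusting for the baseline value alone would not be enough, because a value raised by infection and the same value raised by necrosis have different expected courses.

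**Working it through.** **1. Number per group.** Section 2.8.1 gives mean LVESVi changes of -7.9 and -1.5 mL/m² (difference 6.4), SDs of 11.8 and 11.3, 80% power, α = 0.025, and totals of 108 before and 120 after 10% dropout. Taking α as one-sided and the larger SD:

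n per group = 2 × (1.960 + 0.842)² × 11.8² / 6.4² = 53.4, rounded up to 54. The total is 108, and 108 / 0.9 = 120.

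The plan's figure reproduces. It is used here only to set 54 evaluable patients per group.

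**2. Inputs that the documents do not give (assumptions).**
- f: share of controls infected at the baseline draw, 5% to 50%.
- k: mean excess of the marker in infected patients at baseline, 0.5 to 2 SD. The unit is the SD of change in uninfected patients.
- The excess has fully resolved at 1 year, no SGLT2i patient is infected at baseline, and the drug has no effect.

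**3. Formulas.**
- Extra mean fall in controls: b = f × k.
- Variance of change in controls: 1 + f(1 − f)k². In the SGLT2i group it is 1.
- SE = √{[1 + 1 + f(1 − f)k²] / 54}.
- Chance of a false difference at two-sided 0.05 (normal approximation): Φ(b/SE − 1.96) + Φ(−b/SE − 1.96).

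**4. One case in full (f = 20%, k = 1).** b = 0.20. SE = √(2.16 / 54) = 0.20. b/SE = 1.0. The chance is Φ(−0.96) + Φ(−2.96) = 0.1685 + 0.0015 = 0.17. Almost all of it lies in the direction of a larger fall in controls.

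**5. Range.**

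| Controls infected | Excess (SD) | Extra fall in controls (SD) | Chance of a false difference |
|---|---|---|---|
| 5% | 0.5 | 0.025 | 5.2% |
| 10% | 1 | 0.10 | 8% |
| 20% | 1 | 0.20 | 17% |
| 30% | 1 | 0.30 | 32% |
| 20% | 2 | 0.40 | 44% |
| 50% | 1 | 0.50 | 69% |

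The nominal rate is 5%. The rates apply to one marker tested by a t-type comparison of mean change. If some SGLT2i patients are also infected at baseline, the difference in shares between the groups replaces f in b, and the bias shrinks.

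**The case against.** The strongest reply is that nothing shows the problem to be large. Section 2.3 says only that such patients might go to control, and infection is one of two named examples of a contraindication. The same section says that patients generally stay on their previous glucose-lowering regimen, so a control patient need not have any contraindication. Infected controls could be few, and the first row of the table shows that the bias is then negligible. This stands. A reader might infer that the control group is largely made up of infected patients, or that its markers will fall because infections clear. The documents support neither reading.

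All patients have severe myocardial necrosis (2.2.1), so much of the fall will be infarct-related in both groups. That also stands: the concern is an additional fall in controls. The protocol refers to the presence of infection without calling it active, and it does not say that a genitourinary infection raises all seven markers. Both are clinical premises of this point. Mann–Whitney tests are allowed too, and a shift in means does not carry over to them directly.

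A reader might also take these markers as central to the mechanistic question. The abstract, 2.1 and the Discussion tie mechanism to sST2, Gal-3, FGF21 and miRNA, and Table 2 limits its mechanistic exploratory endpoints to miRNA and FGF21. The inflammation markers are one group of secondary endpoints among several.

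Finally, case-report fields and analysis sets are often left to fuller documents, and the Discussion mentions univariate and multivariate analyses in general terms. This answers only part of the point. The article itself fixes the allocation route, the sampling window and the change endpoint, and it is their combination that creates the bias. Its limitations paragraph does not mention it.

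**Conclusion.** The point holds as a conditional bias in one group of secondary endpoints. Followed as written, the plan lets infection at the index admission affect both the group and the baseline value of infection-sensitive markers, and the unadjusted tests do not separate the two. The expected direction is a larger fall in controls, against an anti-inflammatory effect of SGLT2i.

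The size cannot be derived from the documents. The chance of a false difference stays near the nominal 5% if few controls are infected and the excess is small. It is 17% at 20% infected with a 1 SD excess, and 44% at 20% with 2 SD. These figures rest on assumed shares and excesses, full resolution by 1 year, no infected SGLT2i patients and no drug effect. An estimate in units of a particular marker would have even less support.

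This is one consequence of the wider problem that group depends on contraindication, which also bears on LVESVi. It is worth stating separately because it needs its own data item and its own analysis set.

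**What to change.** - **2.7.1:** record active infection or antibiotic treatment at the existing baseline draw, and again at the 1-year draw.
- **2.4/Table 2 and 2.8.2:** make the main analysis of the inflammation markers the comparison in patients of both groups without infection at the baseline draw, adjusted for baseline value and prespecified confounders. Give the all-patient comparison as supportive.
- **Infection at the 1-year draw:** do not exclude on it. It arises after treatment, and conditioning on it could bring in a new bias. Report it descriptively or use it in a sensitivity analysis.
- **Timing of the baseline draw:** do not delay it in infected patients. That would place their samples later in the post-infarct course than those of other patients and create a timing difference between groups.

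The cost is one case-report item at two existing draws and a changed analysis set for one group of secondary endpoints. Fewer controls will contribute to these markers, so their estimates will be less precise. The allocation rule, the treatments and the LVESVi analysis are not touched.
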